## I. The Need for a Trial

### A. BACKGROUND

#### Atrial Fibrillation (AF) and Stroke Epidemiology

Atrial fibrillation (AF) is a leading cause of stroke, accounting for 15% of strokes overall and 25% of strokes in the elderly. AF-related strokes are more severe, causing long-term physical and cognitive disability and are associated with 50% 1-year mortality. Treatment for stroke is considerable, costing 3.6 billion dollars annually in Canada. The potential burden of AF associated stroke is already a **critical health issue** which will only increase since the prevalence of AF and stroke attributable to AF increases substantially with age; more than 25% of Canadians over the age of 75 will develop AF.

Oral anticoagulation (OAC) is a well-established therapy for stroke prevention. In a meta-analysis, warfarin was shown to reduce the risk of stroke 68% and mortality by 30% compared to placebo. Recent randomized clinical trials have shown that compared to warfarin, new OAC therapies are easier to administer and reduce the risk of stroke/systemic embolism by 23%, total mortality by 11% and intracranial bleeding events by 54%. Despite robust evidence OAC therapy is effective and safe; the availability of simple stroke risk stratification schemes and numerous guidelines providing strong recommendations regarding who would benefit from OAC therapy, less than two-thirds of eligible patients are prescribed OAC therapy. The public health consequence of undertreated AF are enormous, thus, alternative strategies to deliver stroke prevention therapy, such as pharmacist-directed interventions, need to be explored.

#### Expanding Scope of Pharmacist Practice

Pharmacist practices have been evolving over the last century, from managing medication dispensaries to managing drug therapy and prescribing. There are numerous studies demonstrating pharmacist involvement in disease monitoring and optimization of drug therapies for cardiovascular risk factors and heart failure increases adherence to guideline-based targets and improves outcomes. In meta-analyses, pharmacist-directed care or pharmacist collaborative care with nurses or physicians were associated with significant reductions in systolic blood pressure, low-density lipoprotein, improved hemoglobin A1c, and reduced heart failure hospitalizations compared to usual care.

There are several reasons to explain the positive impact of pharmacist involvement: (1) pharmacists are highly accessible; particularly important since physicians are managing a higher prevalence of chronic diseases resulting in patient health care demands that can often exceed their capacity to address them; (2) pharmacists have expertise in drug therapy (pharmacodynamics, pharmacokinetics, drug-drug interactions) allowing for effective and safe drug choices; and (3) pharmacists are consistently ranked as the most trusted professionals allowing them to establish important patient-provider relationships. Given these reasons and rising worldwide health care costs, several countries (United Kingdom, New Zealand, United States, Canada) have recently moved toward various forms of pharmacist independent or collaborative prescribing.

Given traditional means of educating practitioners and patients on better risk factor control have limited effectiveness, a recent Cochrane review concluded that “nurse- or pharmacist-led care may be promising way forward...but these interventions require further evaluation.” In a recent randomized controlled study (PREVENTION led by Co-Investigator [name]) among patients with previous stroke, pharmacist prescribing of anti-hypertensive and lipid lowering drugs led to significantly improved risk factor control compared to a nurse-led disease management control group. In the PREVENTION study pharmacist with prescribing practices evaluated patients independently of their usual pharmacy procedures. In the setting of community pharmacies, pharmacist prescribing of antihypertensive medication alongside their usual clinical practice resulted in a clinically important and statistically significant reduction in blood pressure. Although, pharmacist-led anticoagulation clinics have been shown to improve time in therapeutic range of international normalized ratios, patient satisfaction and quality-of-life, to our knowledge, no randomized trial has compared pharmacists initiation and/or optimization of OAC therapy compared to current practice models in AF patients for stroke prevention in a community setting.

## **B. Can we answer this question?**

We believe we are uniquely placed to answer this question because Alberta was the first province in Canada to allow for additional prescribing authorization and as such pharmacists have the most experience in independent prescribing. According to the Alberta College of Pharmacists, there are 615 prescribing pharmacists to date, an increase of 98% from the prior year, and two-thirds practice in community settings. Pharmacists have the ability to access electronic medical records, order lab tests and interpret results. Importantly, there is a strong track record of pharmacist-led intervention studies conducted by our research group in Alberta.

## **Summary:**

Oral anticoagulation therapy for stroke prevention in AF is safe and effective but under-utilized. Optimal delivery of existing therapies would prevent AF-related stroke. In this study, we will first evaluate pharmacists’ knowledge regarding appropriate use of OAC therapy in AF. We will then evaluate whether active pharmacist intervention could improve evidence-based use of OAC therapy in eligible AF patients. Lastly, we will evaluate the impact of active pharmacist intervention on healthcare utilization to help inform the economic analysis of pharmacist prescribing.

## **C. OBJECTIVES**

### **Primary Objective:**

To determine the difference in proportion of patients receiving optimal OAC therapy at 3 months in those randomized to intervention arm versus control arm.

### **Secondary Objectives:**

(1) To determine the prevalence of patients with unrecognized AF eligible for OAC therapy and those with AF who should be on OAC therapy but are either not on or their existing OAC prescriptions; require adjustment due to contraindications, or sub-optimal levels (hereafter referred to those with “actionable” AF).

(2) To perform a qualitative review of implementation from pharmacists.

(3) To assess patient satisfaction with pharmacist services.

(4) To determine cost of the intervention.

## **D. METHODS**

**Study Design:** This is a pilot prospective, open-label, randomized controlled trial with early versus late pharmacist intervention. The unit of randomization is the patient.

**Study Setting:** The study will be performed in community pharmacies with at least one pharmacist with independent prescribing authority as identified by the Alberta College of Pharmacists as successfully completed requirements and who have access to electronic medical records.

### **Study Population:**

Participants will be eligible for inclusion if they meet the following:

1. Age  $\geq 65$  years with One additional stroke risk factor (hypertension, diabetes, heart failure - history of or left ventricular ejection fraction  $<0.40$ ), previous stroke or transient ischemic attack)
2. AF and not on oral anticoagulation (OAC) therapy but eligible
3. AF on sub-optimal OAC
4. Written informed consent.

### Exclusion criteria

1. AF on optimal OAC therapy
2. Inability to read or understand English
3. Participants considered unreliable by the Investigator or designated pharmacy team member concerning the requirements of follow-up, or with foreshortened life expectancy precluding 3 month follow-up
4. Severe cognitive impairment ( $\geq 5$  errors on the Short Portable Mental Status Questionnaire)

We will identify those with 'actionable' AF (Table 1, Appendix) as those who are found to have AF (either based on single lead ECG or review of medical records), or those with known AF either not on OAC or require prescription adjustment for contraindications or sub-optimal OAC regimen.

**Randomization:** After obtaining informed consent, eligible participants with 'actionable' AF will be randomized to an early versus delayed pharmacist intervention arm using a central randomization number and to preserve concealed allocation.

### **Study Procedure** (Figure 1, Appendix):

#### **(i) Pre-Intervention:**

To aid in the implementation of the study, we will identify local community leaders, and organizations (pharmacists, PCP, local hospitals and community organizations) as part of a stakeholder team. This stakeholder team will meet to discuss study details and address potential barriers. Pharmacists with additional prescribing authority will be provided with training on AF management (symptoms, risk factors, AF-related outcomes, evidence-based guidelines on OAC therapy, bleeding risk) and a pharmacist who specializes in OAC management ([name]) will provide them with

comprehensive training on OAC management. Competency will be assessed after training. The educational seminars can be used to fulfill requirements for continued education.

**Enrollment:** Eligible participants will be recruited using direct advertisement and various in-store strategies (Table 2, Appendix).

The pre-intervention phase of the study will occur in two pharmacies with pharmacists who have additional prescribing authority in a single community and will be a 'run in' to the major clinical trial. The main objective of the pilot phase is to determine capacity and challenges prior to implementation of a larger clinical trial.

Specific Objectives of the pilot phase are:

1. To determine the number of patients recruited and screened
2. To determine time for screening and completion of case report form

## **RCT:**

### **(ii) Intervention: Early versus Delayed (Figure 1):**

Pharmacists will identify eligible participants as 65 years or older AND with one additional risk factor for stroke assessed by brief history and medical record review. The pharmacist will ask about a history of AF and confirm diagnosis by either electrocardiographic (ECG, Holter, event monitor) documentation or by physician documentation (notes or discharge summary). If AF is confirmed and the patient is taking oral anticoagulation appropriately (Table 1, Appendix) then they will be excluded from further participation. Stroke risk factors will also be confirmed based on medical record report or self-report and taking disease-specific medication (Table 3, Appendix).

For participants without a history of AF, the pharmacist will assess rhythm by using a mobile ECG apparatus attached to a smart phone or tablet, which will allow a single lead ECG recording (Alivecor) using two fingers on electrodes for 30 seconds. The single lead ECG recording includes a highly accurate and FDA-approved AF detector (sensitivity 98.5%, CI 92-100% and specificity 91.4%, CI 89-93%). Two ECG recordings will be obtained from each participant and if there is disagreement in the interpretation then a third ECG recording will be obtained. Real-time physician verification will be performed for ECG interpretations of AF. For patients with AF, a 12-lead ECG will be required within 24-48 hours of screening session however randomization will occur based on single lead ECG interpretation.

Participants with unrecognized AF who are eligible for OAC therapy (based on single lead ECG) and those with previously diagnosed AF who should be on OAC therapy but are either not on or their existing OAC prescriptions require adjustment due to, contraindications, or sub-optimal levels will be considered as having 'actionable' AF (Table 1, Appendix).

Participants with 'actionable' AF will be randomized (via a centralized secure website to ensure allocation concealment) in a 1: 1 ratio to either early versus delayed pharmacist intervention after obtaining informed consent.

The early intervention arm will have the following timeline:

[figure not shown]

At time 0, participants will receive AF education, and pharmacists will complete baseline case report form, blood pressure assessment, prescribe OAC therapy or adjust existing prescription based on guideline algorithms; a summary of management will be kept for pharmacy records and a fax will be sent to the family physician regarding participation of the study. At 4 weeks, all participants taking oral anticoagulants will be seen in the pharmacy and the pharmacist/pharmacy technician will complete a follow-up checklist (Figure 4, Appendix). If this is not possible, the participant will be contacted by telephone. As this is a pragmatic trial, additional follow-ups (in-person/phone) will be scheduled at the discretion of the pharmacist particularly if the patient had initiation of warfarin. The OAC clinic at the Mazankowski Heart Institute will provide support throughout this 3 month period if needed. Final follow-up and collection of close-out medications will occur at 3 months. Cardiologist support will be provided for any questions throughout the study period.

For patients randomized to the delayed intervention arm, during the first 3 months they will serve as a control group and will have a fax sent to their family physician identifying them as having 'actionable' AF and a medication list. The delayed intervention arm will follow the same procedures as the early intervention arm for those participants who did not have OAC optimized by their GP during the control phase. The delayed arm timeline will begin at day 90:

[figure not shown]

**(iii) Follow-up:** All participants will have follow-up after 3 months to assess current therapy by a blinded research staff. Follow-up will also entail review of pharmacy electronic records.

**Primary Outcome:** To determine the difference in proportion of patients receiving optimal OAC therapy at 3 months in those randomized to intervention arm versus control arm.

Optimal defined as a new prescription for OAC in a previously untreated AF or known AF who should be on OAC per guideline recommendations or adjustment of an existing OAC in a prescription.

**Anticipated Results:** The rate of new OAC prescriptions or appropriate changes to existing prescriptions will be higher in the intervention arm compared to the control arm.

**Significance:** This study will allow us to determine whether patients randomized to pharmacist intervention have a higher rate of appropriate OAC use compared to usual care. This may also provide early evidence for an expanded role for pharmacists, which includes prescribing of OAC therapy to address stroke prevention in AF.

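### Delayed-arm patients on an anticoagulant that Table 1 flags at any dose for low creatinine clearance have, in the visible text, only a fax with a label and a medication list before day 90

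*Protocol*

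**What the plan says.** **Who is randomised.** Secondary objective 1 includes in 'actionable' AF patients whose existing prescriptions "require adjustment due to contraindications, or sub-optimal levels". The text under the exclusion criteria says the same of those who "require prescription adjustment for contraindications or sub-optimal OAC regimen". Appendix Table 1 gives the detail: among the reasons for adjustment it lists any dose of rivaroxaban or dabigatran at CrCl below 30 ml/min, and any dose of apixaban at CrCl below 25 ml/min. All patients with 'actionable' AF are randomised 1:1, and none of the four exclusion criteria removes this subgroup.

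**What happens next** (Protocol, RCT section (ii)).
- Early arm: the pharmacist prescribes or adjusts the OAC at time 0.
- Delayed arm: "during the first 3 months they will serve as a control group and will have a fax sent to their family physician identifying them". The content of the fax is described as "identifying them as having 'actionable' AF and a medication list".
- Pharmacist procedures then follow for "those participants who did not have OAC optimized by their GP during the control phase", and "The delayed arm timeline will begin at day 90".

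Two other sentences in the section bear on the point: "At 4 weeks, all participants taking oral anticoagulants will be seen in the pharmacy" and "Cardiologist support will be provided for any questions throughout the study period".

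**The concern.** Screening can identify a specific problem, namely a drug that Table 1 accepts at no dose for that patient's renal function. To make that classification the trial staff need the CrCl, and Table 1 prints the formula for it. Yet the only stated communication for a control does not have to include the CrCl or the reason for the flag. The physician receives a general label and a list of drugs.

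The rule also foresees that some physicians will not act, because the delayed intervention is meant for the patients they have not optimised. For most 'actionable' patients, a three-month wait under usual care is the comparison the trial wants to make. For the few on a flagged drug, the wait means continued exposure to something the trial has already identified. What is at stake is the safety of those patients.

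**Working it through.** **1. Are the 'any dose' rows contraindication rows?** Table 1 puts contraindication and sub-optimal levels under one heading and does not label individual rows, so this is an inference. Two things support it. Contraindication is named as a reason for adjustment in secondary objective 1, under the exclusion criteria, in the RCT section and in Table 1. The rivaroxaban and dabigatran rows also accept a reduced dose down to CrCl 30 ml/min and flag every dose below that. The apixaban row bases its dose reduction on age, weight and creatinine, so this second argument does not extend to it.

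**2. Does any stated step reach a control in this subgroup before day 90, other than the fax?**

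| Candidate | What it is | Triggered by the flagged rows? |
|---|---|---|
| 4-week visit | Follow-up checklist, placed in the early-arm paragraph | No, even if it covers both arms |
| Cardiologist support | Available on request | No; someone has to ask |
| B.1 Ethics Approval | General commitment to GCP and Helsinki | No |
| B.2 Patient Confidentiality | Permits sharing information with the patient's physician | No; a permission, not a duty |
| B.1 Risk Benefit Analysis | Bleeding risk of OAC in general | No; subgroup not mentioned |

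**3. How many controls?** The protocol gives no share, so s = 1%, 2% and 5% are assumptions. Planned controls are 370/2 = 185. Controls affected are 185 × s, and the upper limit of exposure is 185 × s × 90 days, reached only if no family physician acts.

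| s | Controls affected | Patient-days, at most |
|---|---|---|
| 1% | 1.85 | 166.5 |
| 2% | 3.70 | 333 |
| 5% | 9.25 | 832.5 |

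The 49% in the sample-size section is a rate of warfarin prescribing after a new AF diagnosis. It is not used here to guess how often a flagged drug would be corrected.

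**4. What would the fix cost in power?** First, the plan's own figure. Inputs from the sample-size section are 49% in the control arm, a 15-point difference (so 64%), 5% alpha and 80% power. Sidedness and the variance formula are not stated. Two-sided with unpooled variance:

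n = (1.960 + 0.842)² × (0.49 × 0.51 + 0.64 × 0.36) / 0.15² = 7.849 × 0.4803 / 0.0225 = 167.5, so 168 per group.

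This matches the plan. The pooled formula gives 171. The unpooled form is therefore inferred from the match. Power at 168 per group is 80.1%.

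In the worst case for contrast, every patient in the subgroup counts as a success in both arms. The rates become 0.49(1 − s) + s and 0.64(1 − s) + s, and the difference is 0.15(1 − s).

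| s | Control | Early | Difference | Power at 168 | n per group for 80% |
|---|---|---|---|---|---|
| 0 | 0.4900 | 0.6400 | 0.1500 | 80.1% | 168 |
| 1% | 0.4951 | 0.6436 | 0.1485 | 79.4% | 171 |
| 2% | 0.5002 | 0.6472 | 0.1470 | 78.7% | 174 |
| 5% | 0.5155 | 0.6580 | 0.1425 | 76.4% | 184 |

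**The case against.** The strongest reply is that this argues from silence. Figure 1, both arm timelines, the 4-week checklist (Figure 4) and the fax form are not in the readable text, and these are where fax content and escalation would normally be set out. That stands: the point is limited to the visible text, and the fix is conditional on it.

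Second, the comparator is deliberate. The sample-size section describes it as an enhanced form of usual care. The flagged prescription predates the trial, and the trial adds notice to the responsible physician. This also stands, and it is why eligibility, randomisation and the comparator should be left alone. Withholding pharmacist prescribing is the comparison; leaving out the reason for a safety flag is not needed for it.

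Third, the 4-week sentence is worded to cover all participants on an OAC. Its position suggests the early arm, but that is not certain. On either reading it is a checklist at week 4, with no stated correction of a flagged drug.

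A reader might also infer more than the documents support:
- *That the fax cannot tell an untreated patient from one on a flagged drug.* The medication list separates the two. What it does not guarantee is the CrCl and the reason.
- *That the protocol bars anyone from warning the physician.* Nothing does; B.2 allows the information to be shared. The gap is that no rule requires it.
- *That both arms need the new rule.* The early arm already adjusts the prescription at time 0.

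**Conclusion.** The point holds as a minor-to-moderate safety matter. Followed as written in the visible text, the protocol allows a control to remain for up to 90 days on a drug that Table 1 flags at every dose, if the family physician does not act on a fax that need not say why action is needed.

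This rests on three things: reading the 'any dose' rows as contraindications, which is natural but not stated; the absence of a further step in Figure 1 or the fax form, which cannot be checked; and a share of affected patients that the protocol does not give. About 2 to 9 of 185 controls would be affected at the assumed 1% to 5%.

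It would be wrong to conclude that the treatment comparison is biased or that the sample size is in error. The plan's 168 per group reproduces, and the design compares the arms it intends to compare. Nor does the point take a position on how these patients should be treated.

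**What to change.** In the delayed-arm paragraph of RCT section (ii), add one sentence to this effect: when a patient meets an 'any dose' CrCl row of Table 1, the family physician is promptly told the drug, the CrCl and the reason for the flag; the contact is recorded; and the patient stays in the intention-to-treat analysis. If Figure 1 or the fax form already contains this step, refer to it in that paragraph. A mention in the Risk Benefit Analysis would be consistent with this. The early-arm text needs no change.

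The administrative cost is one sentence and one recorded contact per affected control. The scientific cost is a slightly more active control arm in this subgroup. In the worst case worked above, power at 168 per group falls from 80.1% to 79.4% at a 1% share or 76.4% at 5%. Holding 80% would take 171 or 184 per group. The loss is smaller to the extent that some of these patients would be counted as successes anyway.

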### **Sample size and Statistical Analysis**

#### **Full trial**

The primary goal of the full is to determine the rate of optimal OAC prescriptions in eligible participants between the active pharmacist arm and enhanced usual care arm. In a prior population-based study performed in Alberta, we found after an initial diagnosis of non-valvular AF 49% of patients were prescribed warfarin within 90 days. We do not have data for a baseline rate for prescribing OAC therapy by pharmacists. Therefore, we surveyed investigators from the C-SPIN to determine the clinically important change in OAC prescribing for an intervention. The consensus was an absolute minimal clinically important difference (MCID) of 15%. If we assume a MCID of 15% (absolute) higher in the intervention compared to control and 1:1 with 80% power at 5% alpha, we will require 168 participants per group. Assuming a dropout or loss to follow-up rate of at least 10%, the sample size will be a total of 370 patients.

All analyses were performed using an intention-to-treat principle of all randomized patients. Descriptive statistics will be used for comparing the two groups across the different outcomes.

